### Subgroup analyses

The following subgroup analyses are planned for the primary outcome of live birth:

#### ᅟ

##### PIP-UE

Type of embryo transfer (fresh or frozen)Number of embryos transferred (single or double)Number of previous embryo transfer procedures not resulting in a clinical pregnancy (for example, 0–1, 2–4, ≥5)Number of embryos transferred previously not resulting in a clinical pregnancy (for example, 0–1, 2–4, ≥5)Timing of endometrial biopsy (for example, follicular phase: cycle prior to embryo transfer cycle, luteal phase: cycle prior to ET cycle, follicular phase: embryo transfer cycle)Major cause of infertility (for example, male factor, endometriosis, ovulatory factor, unexplained, tubal factor, other)History of endometriosis (endometriosis or no endometriosis)Type of IVF (IVF or ICSI)Type of stimulation protocol (for example, long agonist, ultralong agonist, short agonist, antagonist)Duration of infertility (for example, < 2 years, 2–5 years, >5 years)Stage of embryos at transfer (for example, day 5/6 or day 2/3)

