### Timing of randomisation and the study procedure

#### ᅟ

##### PIP-IVF

In PIP-IVF, eligible women will be randomised to the study on or after day one of the cycle that precedes the embryo transfer cycle (Table 1). For example, in participants scheduled for a long course buserelin cycle, randomisation will ideally take place on day one of the cycle, 21 days before down-regulation begins. Women will be informed of their allocation immediately after randomisation. Women randomised to the procedure group will be scheduled to undergo an endometrial biopsy procedure between day three of the cycle preceding embryo transfer and the third day of the embryo transfer cycle. Day one of the embryo transfer cycle is defined as either the day before the first day of controlled ovarian stimulation or day one of a menstrual period/withdrawal bleed for frozen-thaw embryo transfer cycles.

The large window of opportunity to perform the endometrial biopsy procedure is based on results from previous studies. Endometrial injury has been reported to have a beneficial effect as early as the menstrual period of the cycle preceding embryo transfer [20], and as late as the menstrual period following down-regulation [41]. This flexibility is also in keeping with the pragmatic nature of these studies.

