#### Placebo procedure

In PIP-PCOS and PIP-UE, women in the control arm of the trial will undergo a placebo procedure which is designed to blind participants to their allocation. If couples who are attempting to conceive with sexual intercourse are aware of their study allocation, they may purposely or inadvertently influence their pregnancy outcome through behavioural changes, such as a change in sexual frequency or timing.

For the placebo procedure the women will lie in the dorsal or lithotomy position and a speculum will be inserted into the vagina. The biopsy catheter will be placed at the posterior fornix but not inserted into the external os of the cervix. The internal piston is withdrawn and the catheter moved and rotated slightly to replicate the standard biopsy action. The catheter is then removed, followed by the speculum. The catheter is then discarded.

Participants randomised to the control group in PIP-IVF will not undergo any procedure that is additional to standard care.

Shortly following the procedure and before leaving the clinic, participants will be asked to record the pain they experienced during the procedure on a 10 cm VAS. Participants will also be handed an information leaflet detailing what to expect following an endometrial biopsy, and told to seek medical attention and contact the study coordinator if they experience any adverse events that are potentially associated with the procedure, for example, heavy bleeding or signs of infection such as foul smelling discharge.

In PIP-IVF, participants will be contacted within one week of the procedure and asked to report whether they had any vaginal bleeding the day following the procedure. Women in PIP-PCOS and PIP-UE will be asked to complete a study diary for the three study cycles. In this diary they will record the date of the procedure, whether they had any vaginal bleeding the day following the procedure, each day that they have their period and each time they have sexual intercourse during the on-study period. Women will continue to complete the study diary until their third period following the procedure or until confirmation of a clinical pregnancy (that is, all patients have three cycles or opportunities for conception within the on-study period). Participants should be contacted at least once a month to check in and ensure they are completing the study diary and to provide an opportunity to identify any protocol violations.

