##### PIP-UE

Presence of endometriosis (endometriosis or no endometriosis)Timing of endometrial injury (for example, during menstruation or not)Duration of infertility (for example, < 2 years, 2–5 years, >5 years)

For the outcome of pain during the procedure the following subgroup analysis will be performed:Previous cervical surgery (yes or no)Whether a tenaculum was used during the procedure (yes or no)Whether the procedure was performed during menstruation (yes or no).

Subgroup analyses will also be conducted to assess whether the probability of completing the endometrial biopsy procedure (that is, not abandoning the procedure) or needing a tenaculum to complete the procedure, is associated with the age of the woman or whether she had previous cervical surgery.

Any subgroup analyses conducted which are not pre-specified will be clearly stated as ad hoc and will be used for hypothesis generating only.

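### Three of the eleven embryo-transfer subgroups (biopsy timing, number of embryos, embryo stage) do not give a sound randomised contrast in PIP-IVF

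*Protocol article*

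**What the plan says.** All references are to the protocol article.

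- **Purpose of the lists.** Subgroup analyses opens with "The following subgroup analyses are planned for the primary outcome of live birth". Statistical analysis assigns ANOVA or logistic regression to the pre-specified subgroup effects.
- **The three items.** The first list, headed PIP-UE, contains eleven items. Among them are "Timing of endometrial biopsy (for example, follicular phase: cycle prior to embryo transfer cycle" (with two further timing levels), "Number of embryos transferred (single or double" and "Stage of embryos at transfer (for example, day 5/6 or day 2/3".
- **The control arm.** Under Placebo procedure: "Participants randomised to the control group in PIP-IVF will not undergo any procedure that is additional to standard care". The Blinding section describes PIP-IVF as open label.
- **Order of events.** Under the timing section for PIP-IVF, "eligible women will be randomised to the study on or after day one of the cycle that precedes the embryo transfer cycle". Women learn their allocation at once, and the biopsy is then scheduled "between day three of the cycle preceding embryo transfer and the third day of the embryo transfer cycle". Table 1 places the recording of IVF cycle characteristics at the IVF cycle and embryo transfer.
- **Denominator.** Outcomes defines live birth per woman randomised.
- **Stratification.** Randomisation in PIP-IVF is stratified by clinic and by fresh or frozen-thaw transfer.

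**The concern.** A treatment-effect subgroup needs a variable that is defined in both arms and cannot be changed by allocation. Biopsy timing fails the first condition, because half the trial has no biopsy. Number and stage of embryos at transfer are at risk on the second: they become known only after the woman and her clinic know the allocation, and they never become known for a woman who has no transfer.

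What is at stake is how these results would be read. The Methods/design section defends the wide biopsy window as pragmatic and hopes to detect effects in different subgroups. The Background reports a detrimental effect when the injury was done on the day of oocyte retrieval. Readers will therefore look to the timing result. If it appears beside true baseline subgroups, a non-randomised comparison could be taken for evidence that one timing works better than another.

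**Working it through.** **Plan's own figures.** The plan gives no figure for these three subgroups. The only number tied to subgroups is the PIP-IVF size of 188 per arm, doubled for the fresh/frozen split. With 33 % vs 17 %, two-sided 5 % and the pooled formula n = [1.960·√(2·0.25·0.75) + z·√(0.33·0.67 + 0.17·0.83)]² / 0.16², 90 % power (z = 1.282) gives 152 and 95 % power (z = 1.645) gives 188. That mismatch with the stated 90 % is a separate matter, and nothing below depends on it.

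**Step 1: sort the eleven items.**

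| Status | Items | Count |
|---|---|---|
| Stratum, or fixed before randomisation | fresh/frozen; previous failed transfers; embryos previously transferred without pregnancy; main cause of infertility; endometriosis history; duration of infertility | 6 |
| Undefined in controls | biopsy timing | 1 |
| Observed after allocation | number of embryos; stage at transfer | 2 |
| No defect argued here; may be planned at randomisation | IVF or ICSI; stimulation protocol | 2 |

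**Step 2: biopsy timing.** Let A = 1 for biopsy and let T1, T2, T3 mark the three timing levels. An interaction model is logit(p) = β0 + β1·A + Σγk·Tk + Σδk·A·Tk. Because Tk can be 1 only when A = 1, Tk and A·Tk are the same column, so γk and δk cannot be separated. Among women with a completed biopsy T1 + T2 + T3 = A, so β1 is aliased too. Only the sum β1 + γk + δk can be estimated, which is level k against all controls. The date is scheduled after allocation, so that comparison, like one between levels, is not randomised. Controls available per level: 0, 0, 0.

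**Step 3: number of embryos, with no true treatment effect.** All inputs are assumptions except two anchors from the protocol: an average live birth rate of 17 % (Sample size, lower rate) and double transfer in at most 20 % of women (PIP-IVF inclusion criteria). Half the women have good prognosis (25 %) and half poor (9 %), average 17 %. In controls, 10 % of good- and 30 % of poor-prognosis women have a double transfer, 20 % overall.

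- Controls, single: (0.70·0.09 + 0.90·0.25) / 1.60 = 0.180.
- Controls, double: (0.30·0.09 + 0.10·0.25) / 0.40 = 0.130.

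Now let allocation change only the double-transfer share among poor-prognosis women in the biopsy arm:

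| Share, biopsy arm | Single: rate, RR | Double: rate, RR |
|---|---|---|
| 30 % (no shift) | 0.180, 1.00 | 0.130, 1.00 |
| 25 % | 0.1773, 0.985 | 0.1357, 1.04 |
| 20 % | 0.1747, 0.971 | 0.1433, 1.10 |
| 10 % | 0.170, 0.944 | 0.170, 1.31 |

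The apparent effect comes only from the shift. Other shifts would give other sizes and could reverse the direction. The same logic applies to stage.

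**Step 4: women without a transfer.** If a fraction f of each arm has a transfer and live births arise from transfers, the rate per transfer is p/f and the risk ratio is (pT/fT)/(pC/fC) = (pT/pC)·(fC/fT). With fT = fC the ratio is unchanged. With unequal f it is not, and in either case the estimate no longer refers to women randomised.

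**The case against.** The case against is substantial on several points, and most of it stands as a limit on the concern.

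- A reader might infer that the whole list is unusable. The documents do not support that: at least six of the eleven items are fixed before randomisation or are the stratum.
- A reader might infer that number and stage are necessarily biased. They are not. The risk ratio stays at 1.00 if allocation changes neither the choice nor the chance of transfer. Double transfer is tied to clinic practice and randomisation is stratified by clinic, which lowers the risk without removing it. For frozen-thaw transfers stage may largely be settled beforehand, although the protocol does not say so.
- A reader might infer from the wrong heading, together with "Any subgroup analyses conducted which are not pre-specified will be clearly stated as ad hoc", that the fresh/frozen analysis is ad hoc. Sample size for PIP-IVF already announces it, so that reading fails. The heading is an evident slip: PIP-UE women should have no fertility treatment and have their own list later.
- A reader might take fresh/frozen as the transfer actually done. The text does not say so, and the stratum is the natural meaning. One sentence would settle it.
- A higher rate per transfer than per woman randomised is not in itself bias, as Step 4 shows.
- Timing may have been meant as a description within the biopsy arm, since the same section uses the term subgroup for questions about completing the procedure. That is possible, but the item stands among analyses of live birth and no such restriction is stated.

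The timing objection does not extend to PIP-UE or PIP-PCOS, where sham controls have a procedure date.

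**Conclusion.** The concern holds for three items. For biopsy timing the defect is structural and needs no assumption: no control has a value, so no effect by timing can be estimated, and any available comparison is non-randomised. For number and stage of embryos the contrast can be computed, but it conditions on something observed after open-label allocation and leaves out women without a transfer. It is unbiased only if allocation affects neither the choice nor the chance of transfer. The illustrated distortion for number of embryos, risk ratios of 0.944–0.985 (single) and 1.04–1.31 (double) with no true effect, rests on assumed prognoses and shifts. It shows that bias is possible and does not predict its size. The baseline subgroups and the primary intention-to-treat analysis are unaffected.

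**What to change.** 1. **Biopsy timing.** Report actual timing only as a descriptive, exploratory analysis within the biopsy arm, with no treatment-effect claim. Alternatively, where available, use an intended window recorded in both arms before allocation is revealed.
2. **Number and stage of embryos.** Define both by the plan recorded at randomisation, for all women randomised, or label them exploratory post-randomisation analyses.
3. **Fresh/frozen.** State that it is taken from the randomisation stratum.
4. **Heading.** Change the heading of the first list from PIP-UE to PIP-IVF.

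The cost is wording in the protocol and analysis plan and, if planned values are used, a few fields on the randomisation form. The expected first day of the transfer cycle is already recorded there. There are two downsides. Planned and actual treatment will differ for some women. Recruitment began in June 2014, so planned values may be unavailable for women already randomised; for them the exploratory label should apply, because plans reconstructed after open allocation would not be free of bias.

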##### PIP-PCOS

The type of ovulation induction medication the participant was on when they conceived (for example, clomiphene, letrozole, metformin, FSH and each combination used)Number of previous ovulatory ovulation induction cycles (for example, 0–2, 3–6, >6)Presence of endometriosis (endometriosis or no endometriosis)Timing of endometrial injury (for example, during menstruation or not)

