### Outcomes

The primary outcome is live birth rate per woman randomised, as defined previously [35].

Secondary outcomes include:ongoing pregnancy per woman randomised (defined as continuing pregnancy diagnosed by ultrasonographic visualisation of one or more gestational sacs on or after 12 weeks gestation)clinical pregnancy per women randomised (defined as a pregnancy diagnosed by ultrasonographic visualisation of one or more gestational sacs, including ectopic pregnancy)biochemical pregnancy (defined as βhcg > 25 mIU/ml) PIP-IVF onlymultiple pregnancies per women randomised and per clinical pregnancy (defined as ultrasonographic visualisation of two or more gestational sacs or heartbeats)ectopic pregnancy per women randomised and per clinical pregnancy (defined as a pregnancy in which implantation takes place outside the uterine cavity)miscarriage per women randomised and per clinical pregnancy (defined as the spontaneous loss of a clinical pregnancy before 20 completed weeks of gestational age)neonatal characteristics (for example, gender, gestation at birth, malformations)placenta characteristics (placenta previa: major, placenta previa: minor, placental abruption, placenta accreta: previous uterine surgery, placenta accreta: no previous uterine surgery)pain during the procedure (as measured by a 10 cm visual analogue scale (VAS))bleeding the day following the procedure.

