### Standard care

Standard care will be identical in both arms of each PIP study. The PIP studies are pragmatic trials, and standard care may differ slightly between participating centres. For example, some centres may prefer an antagonist protocol and others may prefer a long course agonist protocol for IVF cycles.

Participants in PIP-IVF are either taking part in an IVF/ICSI cycle involving controlled ovarian stimulation, oocyte collection and fresh embryo transfer, or are planning a frozen-thaw embryo transfer. Any IVF protocol or use of additional treatments, such as pre-implantation genetic diagnoses or assisted hatching, is acceptable. Similarly, artificial, manufactured and natural cycles for frozen-thaw embryo transfers are acceptable.

PIP-PCOS participants are on ovulation induction medication: clomiphene, letrozole, follicle-stimulating hormone (FSH) or metformin. The choice of medications, dosages and combinations of medications may vary.

Participants in PIP-UE should not be on any fertility treatment. Participants in PIP-PCOS and PIP-UE are asked not to undergo any additional fertility treatment; for example, IUI and IVF are considered protocol violations. Vitamins, dietary supplements and other medications or procedures which are not normally considered fertility treatments, such as acupuncture, are permitted in all studies.

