### Eligibility assessment

Potentially eligible women will be informed about the PIP study by invitation letter, advertisement (for example, poster or newsletter) or their treating clinician or nurse. All potential participants will have the opportunity to ask questions about the study and discuss any concerns or queries prior to making a decision about whether to take part. Informed consent will be obtained from all participants in writing prior to their recruitment. Informed consent will be undertaken by a PIP study researcher who is familiar with the study details and has adequate training and experience in trial recruitment (see Tables 1 and 2).

**Table 1 Tab1:** Schedule of procedures and outcome measurements for PIP-IVF

	Pre-study	Day 1 of prior cycle	Day 3 of prior cycle-day 3 of IVF/embryo transfer cycle	Day after procedure	IVF cycle/embryo transfer	About 2 weeks after embryo transfer	About 6 weeks gestation	≥12 weeks gestation	Birth
Eligibility screen	x								
Informed consent	x								
Randomisation		x							
Endometrial scratching (intervention group only)			x						
Pain (VAS) (intervention group only)			x						
Adverse events (intervention group only)			x	x					
Bleeding (intervention group only)				x					
IVF cycle characteristics					x				
Biochemical pregnancy						x			
Clinical pregnancy							x		
Ongoing pregnancy								x	
Live birth									x

**Table 2 Tab2:** Schedule of procedures and outcome measurements for PIP-UE and PIP-PCOS

	Pre-study	Day 1-12 of cycle 1	Day after procedure day	End of study/end of cycle 3	About 6 weeks gestation	≥12 weeks gestation	Birth
Eligibility screen	x						
Informed consent	x						
Randomisation		x					
Study intervention		x					
Pain (VAS)		x					
Adverse events		x	x				
Bleeding			x				
Cycle characteristics (e.g., intercourse frequency, ovulation medication dose (PIP-PCOS only), via study diary)				x			
Clinical pregnancy					x		
Ongoing pregnancy						x	
Live birth							x

The details of all women assessed for eligibility will be recorded to ensure reporting as per the CONSORT statement [40]. This record will include reasons for ineligibility or nonparticipation.

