##### PIP-PCOS and PIP-UE

Participants in PIP-UE and PCOS are asked to try to conceive for three cycles: the cycle in which they undergo the study procedure and the two following cycles. Participants remain in the study until they either achieve a clinical pregnancy or get their third menstrual period following the procedure. This means that each participant has three cycles whilst on the study where they have the opportunity to conceive. For PIP-PCOS women this time frame is constant regardless of whether the cycles are ovulatory or not. The three study cycles are defined as the on-study period (Fig. 3).

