### Statistical analysis

Demographic and baseline data will be compared between the two groups using the chi-squared test or *t*-test. Outcome data for the primary analyses will be treated in an intention-to-treat manner, such that all participants remain in the groups to which they were randomised. If no outcome data is available for the primary outcome of live birth, this will be imputed to assume that women with no outcome data did not have a live birth. Sensitivity analyses based on different assumptions may be used for secondary analyses. Per protocol analyses will be conducted as a secondary analysis.

For binary outcomes (for example, live birth), risk ratios will be calculated with associated 95 % confidence intervals and *p* values. ANOVA or logistic regression analysis will be used for the analysis of pre-specified subgroup effects. For continuous outcomes (such as pain), the mean difference will be calculated and the student’s *t*-test will be used.

Assessment of participant blinding will be performed using both James’ and Bang’s blinding indices [47, 48]. All statistical analysis will be performed using STATA or a similar statistical programme.

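### The PIP-PCOS medication subgroup is defined by the drug in use at conception, so women who do not conceive cannot be classified and the effect on live birth per woman randomised cannot be estimated within it

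*Protocol article*

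**What the plan says.** Four statements in the Protocol article bear on this point.

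- **Outcome of the subgroup analyses** (Subgroup analyses): "The following subgroup analyses are planned for the primary outcome of live birth".
- **Denominator** (Outcomes): "The primary outcome is live birth rate per woman randomised". Under Statistical analysis, "all participants remain in the groups to which they were randomised", and a woman without outcome data is counted as having no live birth.
- **Subgroup variable** (Subgroup analyses, PIP-PCOS, first item): "The type of ovulation induction medication the participant was on when they conceived", with single drugs and each combination as the example categories.
- **Method** (Statistical analysis): "ANOVA or logistic regression analysis will be used for the analysis of pre-specified subgroup effects".

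Two further statements matter. Standard care says of the PIP-PCOS drugs that "The choice of medications, dosages and combinations of medications may vary". The on-study period for PIP-PCOS and PIP-UE is fixed by this rule: "Participants remain in the study until they either achieve a clinical pregnancy or get their third menstrual period following the procedure". A woman who conceives therefore leaves early, and a woman who does not conceive contributes all three cycles.

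**The concern.** A subgroup variable for a randomised comparison needs a value for every randomised woman, and that value should not depend on what happened after randomisation. This variable meets neither condition. It is read at conception, so it exists only for women who have already passed the step that the procedure is meant to influence.

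The analyst then has three ways forward, none of them stated in the protocol:

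1. Analyse only women with a value. All of them conceived, so the comparison is of pregnancy loss between arms.
2. Give the others a separate category for not having conceived. No woman in it can have a live birth, so it carries no information on the treatment effect.
3. Substitute another drug, such as the last one used. The variable then depends on how long the woman stayed in the study, and so on her outcome.

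What is at stake is whether the effect of endometrial injury differs by induction drug. The Methods/design section gives the detection of effects in different patient subgroups as a benefit of the broad population. The protocol also reserves the hypothesis-generating label for subgroups that are not pre-specified, so this result would carry pre-specified status.

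**Working it through.** The protocol states no figure for this subgroup. The check is therefore of the definition, followed by its size under the design assumptions.

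**Inputs**
- Live birth of 5 % (sham) and 12 % (biopsy) per cycle: Sample size, PIP-PCOS.
- Three cycles: on-study period.
- 280 women, 1:1, so 140 per arm: Sample size and Randomisation. The stated inflation reproduces: 252 / 0.90 = 280.
- Live births 19 % lower than pregnancies, ratio 0.81: Sample size, PIP-UE. Its use for PIP-PCOS is an assumption.

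**The protocol's own method, reproduced for PIP-UE.** 1 − 0.97³ = 8.7 % and 1 − 0.91³ = 24.6 %, which it gives as 9 % and 25 %. Multiplying by 0.81 gives 7.3 % and 20.3 %, which it gives as 7 % and 20 %. The same two steps are applied below to PIP-PCOS.

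**Step 1. Live birth over three cycles.** Sham: 1 − 0.95³ = 14.3 %. Biopsy: 1 − 0.88³ = 31.9 %. Risk ratio per woman randomised: 0.3185 / 0.1426 = 2.23.

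**Step 2. Women with a value.** Sham: 0.1426 / 0.81 = 17.6 %. Biopsy: 0.3185 / 0.81 = 39.3 %.

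**Step 3. Women without a value.** Sham: 82.4 %, about 115 of 140. Biopsy: 60.7 %, about 85 of 140. Together that is about 200 of 280, a little over 71 %. Dividing each cycle's rate by 0.81 before compounding gives 82.6 % and 61.8 %, about 202 of 280.

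Range for the assumed ratio: at 1.00 (no loss) the unclassified shares are 85.7 % and 68.1 %. At 0.70 they are 1 − 0.1426/0.70 = 79.6 % and 1 − 0.3185/0.70 = 54.5 %. Throughout this range more than half of each arm is unclassified, and the arms differ.

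**Step 4. Effect among women with a value.** With equal loss in both arms, live birth given conception is 0.81 in each, so the risk ratio is 0.81 / 0.81 = 1.00. A simulation of 2,000,000 women over three cycles, with the same effect in two medication groups, agrees:
- Overall risk ratio per woman randomised: 2.19.
- Within medication group, conceivers only: 1.002 and 0.999.
- Within medication group, all randomised women classified independently of outcome: 2.20 and 2.18.

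**Step 5. Substituting the last drug used (illustration only).** Assume two equally effective drugs at 5 % per cycle, 60 % starting on A and 40 % on B. After cycles 1 and 2, 30 % of those who failed on A switch to B. None of these shares is in the documents.

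- Cycle 1: A 0.600, 0.0300 conceive, 0.570 fail, 0.171 switch. B 0.400, 0.0200 conceive, 0.380 fail.
- Cycle 2: A 0.399, 0.0200 conceive, 0.379 fail, 0.114 switch. B 0.551, 0.0276 conceive, 0.523 fail.
- Cycle 3: A 0.265, 0.0133 conceive. B 0.637, 0.0319 conceive.
- Last drug A: 0.0632 conceptions among 0.3153 women, 20.1 %. Last drug B: 0.0794 among 0.6847, 11.6 %.

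With no switching both groups show 1 − 0.95³ = 14.3 %, and the distortion is zero.

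**The case against.** The strongest reply is that this is loose wording in one of four PIP-PCOS subgroups. The intended variable was probably the medication used in the study cycles. Table 2 lists "ovulation medication dose (PIP-PCOS only), via study diary" among the cycle characteristics and does not limit it to women who conceive, so a usable variable might be derived before analysis. The primary estimate, sample size and randomisation are untouched. This stands as an argument on severity. It does not repair the definition, because no section gives a category to a woman who does not conceive. Nor is this a detail left to an analysis plan: the protocol states the definition, and a plan that followed it would carry the fault forward.

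It is also fair to say that the last-drug rule is not in the protocol, and that the switching shares above have no source. Standard care says that medication may vary, but not that women change drugs during the study. The illustration compares drugs and has no trial arms, so it does not measure bias in the treatment-by-medication interaction. It shows only that the substitute depends on the outcome when women switch.

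A reader might go further and infer that any drug difference found would be an artefact, or that the procedure itself changes prescribing. The documents support neither. Under a last-drug rule the distortion depends on how much switching occurs. The procedure could at most change the time to conception, and through it the chance of a later switch.

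**Conclusion.** The point holds. The subgroup as defined cannot yield a treatment effect on live birth per woman randomised. Under the design rates and the borrowed 0.81 ratio, about 82 % of sham and 61 % of biopsy women have no value. Among those who do, a risk ratio of about 2.2 falls to about 1.0. The first result depends on the assumed ratio within the range shown, and the second on equal pregnancy loss in the two arms. If loss differed, the ratio among conceivers would reflect that difference, and still not the effect on conception. That the variable is undefined for non-conceivers needs neither assumption.

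The illustrative 20 % against 12 % under a last-drug rule is a possible size, not an estimate. A reader might infer that the trial's main result is compromised; it is not. This is a pre-specified secondary subgroup that should be corrected, and the primary analysis is unaffected.

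**What to change.** Redefine the first PIP-PCOS subgroup as the ovulation induction medication (drug or combination) in use or planned for study cycle 1, as recorded at randomisation. Test it as a treatment-by-medication interaction on live birth per woman randomised, with all women kept in their allocated arms. Report the medication in the conception cycle only as a description of the pregnancies.

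The cost is one sentence in the protocol or analysis plan, plus confirmation that the database holds the cycle 1 drug for every woman. Randomisation takes place at the clinic visit, on days 1 to 12 of an ovulation induction cycle, so the information is available then. No treatment, dose or visit changes. The amendment should be dated before outcomes are examined by arm.
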